## Abstract

**Background:**

Transaortic transcatheter aortic valve implantation (TAo-TAVI) is a recently developed approach that provides an alternative delivery route for valve replacement in patients with vascular abnormalities or existing comorbidities. While initial studies have shown the principal efficacy and safety, the real world effectiveness and safety of this approach remains to be fully assessed.

**Methods/Design:**

In this regard, the *Registry Of the Utilization of the TAo-TAVI approach using the Edwards SAPIEN Valve* (ROUTE) represents the first multicenter, multinational prospective documentation of the course and outcome of patients with severe calcific aortic stenosis (AS) undergoing TAo-TAVI. ROUTE commenced in February 2013 with the goal of consecutively enrolling 300 patients at up to 22 sites across Europe. The primary objective of ROUTE is to determine the 30-day mortality associated with TAo-TAVI using the Edwards SAPIEN THV (Edwards Lifesciences, Irvine, CA). In addition, ROUTE aims to quantify complications, predictors of patient outcome and the value of CT guided valve sizing.

**Discussion:**

Findings from this landmark registry will provide important information regarding procedural success rates and early mortality in patients undergoing TAo-TAVI.

**Trial registration:**

Identifier:
NCT01991431.

## Background

Aortic stenosis (AS) is a disease characterized by progressive narrowing of the aortic heart valve and is most frequently caused by age-related calcification. At 75 years of age 4.6% of the adult population displays severe AS
[1], and at 85 years old this prevalence increases to 8%
[2]. Thus, calcific AS represents the most common form of valve disease in the Western world, constituting a significant healthcare burden
[1, 3]. The 1-year and 5-year survival rates for untreated patients with AS were reported to be 62% and 32%, respectively
[4].

Therefore, severe symptomatic AS is considered to be a class I indication for aortic valve replacement surgery
[5], a treatment that has demonstrated good efficacy and safety
[6, 7]. Nevertheless, it has been suggested that 30–40% of elderly patients are never offered surgical intervention for AS due to advanced age, comorbidities and high surgical risk
[3, 8]. In this regard, transcatheter aortic valve implantation (TAVI) has emerged as a viable alternative to conventional valve replacement in patients for whom open heart surgery is not suitable
[9]. For this reason, the TAVI technique has gained popularity since it was first described by Cribier et al.
[10, 11], yielding promising clinical results over time
[12–14]. In fact, a recent randomized clinical trial revealed a 20% reduction in the all-cause mortality associated with the use of TAVI in comparison to medical therapy in patients unsuitable for conventional surgery
[15].

The Edwards SAPIEN transcatheter heart valves (THV) (SAPIEN XT, SAPIEN 3) are commercially available devices for performing TAVI, and can be introduced into the body via transfemoral (TF), transapical (TA) or trans-subclavian routes
[12, 13, 16, 17]. However, in some cases TF and/or TA delivery are impossible due to anatomical abnormalities or existing comorbidities (e.g., respiratory disease or decreased left ventricular function). Therefore, a primary goal related to refining such devices has been to improve deliverability in order to reduce patient mortality and morbidity. In this regard, transaortic (TAo) implantation has been shown to be feasible and safe in patients
[18–20], and TAo delivery of Edwards SAPIEN valves was recently approved in Europe. Nevertheless, the approach remains to be evaluated, and further study is required to fully assess the efficacy and applicability of the TAo-TAVI procedure. Indeed, it remains unclear which patients may show the most benefit or risk associated with TAo-TAVI.

*The Registry Of the Utilization of the TAo-TAVI approach using the Edwards SAPIEN Valve (ROUTE)* represents the first multicenter, multinational prospective study to investigate the course and outcome of patients with symptomatic severe calcific AS undergoing TAo-TAVI with the SAPIEN XT and SAPIEN S3 THVs. ROUTE is an ongoing study, which commenced in 2013 to determine the 30-day mortality rate associated with TAo-TAVI using Edwards SAPIEN XT and SAPIEN 3 THV. ROUTE should provide essential data regarding procedural success rates and early mortality in patients undergoing TAo-TAVI.

## Methods/Design

### The design of route

ROUTE is an international multicenter, prospective, observational registry with consecutive patient enrollment at up to 22 sites across Europe. Ethical approval has been obtained at the ethics committee responsible for each site prior to patient enrollment. All patients are required to provide written informed consent prior to study participation. The investigation commenced in February 2013. The registry is registered at www.clinicaltrials.gov, Identifier: NCT01991431.

### Site selection

Sites are selected based on their TAo access experience in different countries across Europe (France, Italy, Netherlands, United Kingdom, Poland, Finland, Denmark, Norway, Germany, and Austria). They are required to have preliminary experience with TAo-TAVI (i.e., minimum of five prior implantations).

Sites were, independent of this registry, trained in the transaortic implantation of transcatheter heart valves in accordance with the manufacturer’s instructions (Edwards Lifesciences, Irvine, CA). Exhaustive fundamentals training was conducted (i.e., didactic sessions, case observations, device preparation, simulator training) along with on-site training, which was consistent with the Edwards Standard Operating Procedure.

### Patients selection

Patients can be included in ROUTE if they display symptomatic severe calcific AS and are scheduled to receive TAo-TAVI using an Edwards SAPIEN THV (SAPIEN XT or SAPIEN 3) irrespective of the feasibility of other access routes. Also, subjects are required to present an estimated operative/procedural mortality risk of ≥15% as assessed by the Logistic EUROSCORE I or 10% STS-PROM according to the IFU of the Edwards SAPIEN THVs. However, patients showing any of the following contraindications to the procedure are excluded from the study: (1) congenital unicuspid/bicuspid aortic valves; (2) evidence of an intracardiac mass, thrombus, vegetation, active infection, or endocarditis; (3) inability to tolerate anticoagulation/antiplatelet therapy; and/or (4) excessive calcification of the aorta at the access site. In addition, those patients receiving TAo-TAVI in combination with another procedure (e.g., TAo-TAVI plus coronary artery bypass graft) are excluded.

### Enrollment and data collection

ROUTE aims at enrolling 200 consecutive patients at a rate of approximately 2–3 subjects a month per site (6–10 patients competitively enrolled per site). Patient data must be collected at the time of valve implantation (baseline), intervention, discharge, and 30 days post procedure (i.e., ≥23 days and <37 days) (Table 
1). Complication rates are reported according to the Valve Academic Research Consortium-2 (VARC 2) criteria
[21].

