### Statistics

The sample size for ROUTE was estimated based on an overall mortality rate of approximately 7.1% at 30 days in accordance with unpublished data provided by the principal investigators. This rate can be ascertained with a 95% CI of 7.1 ± 3.56%. 95% confidence intervals are ±2.36 and ±3.02 at 3.0 and 5.0% risk respectively while they are ±3.97 and ±4.34 at 9.0 and 11.0%.

Intent-to-treat analysis, defined as all patients enrolled in the registry will be evaluated. Subjects are considered registry participants when they enter the cath lab/hybrid suite. Descriptive data summaries will be used to present and summarize the collected evaluation data. For categorical variables (e.g. gender) frequency distributions will be given. For numeric variables (e.g. patient age) minimum, maximum, mean, median and standard deviation will be calculated.

Linearized rates and actuarial probability statistics will be used when appropriate for adverse event reporting, and Kaplan–Meier plots may be employed for survival and outcome analyses.

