### Amendments/Notes to file

The protocol which initially was confined to the documentation of the Edwards SAPIEN XT valve was opened in February 2014 to allow the documentation of the Edwards SAPIEN3 valve. In June 2014 the patient number to be enrolled was increased by 100 resulting in a total of 300 enrolled patients and about 150 patients per valve.

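### The enrolment paragraph still carries the old target of 200 and a per-site expectation of 6–10, neither of which fits the current goal of 300 at up to 22 sites

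*Protocol article*

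**What the plan says.** The protocol article gives the enrolment target in three places.

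- *Enrollment and data collection* (Methods/Design), in the present tense: "ROUTE aims at enrolling 200 consecutive patients at a rate of approximately 2–3 subjects a month per site (6–10 patients competitively enrolled per site".
- *Abstract, Methods/Design*: the registry started in February 2013 "with the goal of consecutively enrolling 300 patients at up to 22 sites across Europe".
- *Amendments/Notes to file*, on a change dated June 2014, reports: "the patient number to be enrolled was increased by 100 resulting in a total of 300 enrolled patients and about 150 patients per valve".

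*The design of route* repeats the limit on sites: "consecutive patient enrollment at up to 22 sites across Europe".

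The *Statistics* section bases the sample size on an "overall mortality rate of approximately 7.1% at 30 days". It gives a 95% confidence interval half-width of ±3.56 points at that rate, and half-widths at four other rates, but it names no number of patients.

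**The concern.** Two different totals stand in the article as the current aim. This is more than a difference between an amendment log and the text it replaced, because the abstract and the enrolment section disagree even if the amendments section is set aside. Nor can the Methods be read as a record of the protocol as first written. *Patients selection* already admits both valve types, and the amendments section says the second valve was added only in February 2014. The Methods were updated for that change but not for the increase in June 2014.

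The per-site figure has the same problem. Replacing 200 with 300 alone would leave a paragraph whose site count and per-site expectation do not multiply up to its own target.

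In a single-arm registry whose primary result is one proportion, the number enrolled sets both the precision of that result and the point at which enrolment ends. Both should be stated once and consistently.

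**Working it through.** **Inputs.** Sites: up to 22 (abstract; *The design of route*). Per site: 6–10 patients, at 2–3 a month (*Enrollment and data collection*). Targets: 200 (same section) and 300 (abstract; *Amendments/Notes to file*). Assumed 30-day mortality: 7.1%, with a half-width of ±3.56 points (*Statistics*).

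**Step 1: which number of patients the stated precision belongs to.** The article names no formula. The usual large-sample half-width, 1.96 × √(p(1−p)/n), reproduces all five stated figures at n = 200. For p = 0.071: 1.96 × √(0.071 × 0.929 / 200) = 3.56 points.

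| Assumed mortality | Stated half-width | n implied by it | Half-width at n = 200 | Half-width at n = 300 |
|---|---|---|---|---|
| 3.0% | ±2.36 | 200.7 | ±2.36 | ±1.93 |
| 5.0% | ±3.02 | 200.1 | ±3.02 | ±2.47 |
| 7.1% | ±3.56 | 199.9 | ±3.56 | ±2.91 |
| 9.0% | ±3.97 | 199.6 | ±3.97 | ±3.24 |
| 11.0% | ±4.34 | 199.7 | ±4.34 | ±3.54 |

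So the Statistics section, like the enrolment paragraph, still describes 200 patients.

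**Step 2: what the per-site range adds up to.**

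- Low end: 22 × 6 = 132.
- High end: 22 × 10 = 220.
- Average needed for 200: 200 / 22 = 9.1 per site, inside 6–10.
- Average needed for 300: 300 / 22 = 13.6 per site, above 10.
- Gap at the high end: 300 − 220 = 80 patients, or 80 / 300 = 27%.
- Sites needed for 300 at 6–10 each: 300 / 10 = 30 to 300 / 6 = 50, against a maximum of 22.

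Because 22 is an upper limit, 13.6 is the smallest average that reaches 300. With 20 sites, for example, it would be 300 / 20 = 15.

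**Step 3: whether the monthly rate is the obstacle.** 22 sites at 2–3 a month enrol 44–66 patients a month. 300 / 66 = 4.5 months and 300 / 44 = 6.8 months. The rate does not stand in the way of 300; only the total and the per-site range are out of line.

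**The case against.** The strongest reply is that the article resolves the conflict itself. The amendments section gives the date, the increase and the new total, and it agrees with the abstract, so someone who reads the whole article can tell that 300 is meant. This stands: the intended target is not in doubt. It does not correct the enrolment paragraph, which still states a different number as the current aim.

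The second reply concerns the per-site range. A reader might infer from 132–220 that 300 cannot be reached, or that each site stops at ten and later eligible patients are left out, which would break consecutive enrolment. The documents do not support either inference. Competitive enrolment normally means that sites recruit towards a shared total and that faster sites contribute more, so 6–10 reads as an expectation. No sentence sets a maximum per site, and enrolment is described as consecutive in all three places where it is mentioned. The timing does not settle the matter either. At 2–3 a month a site would pass 6–10 patients in 2 to 5 months, yet the total was raised in June 2014, 16 months after the start. Staggered site opening, slower accrual or a non-binding range would each explain that.

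Third, the stated precision would be met at either total: ±3.56 points at 200, ±3.39 at 220 (1.96 × √(0.071 × 0.929 / 220)) and ±2.91 at 300. This also stands, so the primary estimate does not fall below its stated precision. The figure printed is nevertheless not the one that belongs to the current target. The goal of about 150 patients per valve would not be met at 220 (about 110 each on an even split), but the *Pre-defined endpoints* section lists no separate objective by valve, so little weight rests on that.

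**Conclusion.** The point holds as an inconsistency in current text. The enrolment paragraph states a superseded target and a per-site expectation that matches only that target. On the article's own planning figures the range falls at least 80 patients (27%) short of 300, and 300 needs an average of at least 13.6 per site. The precision statement is likewise that of 200 patients: ±3.56 points at 7.1% against ±2.91 at 300, a difference of 0.65 points in half-width.

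This rests on three assumptions: that all 22 sites enrol (fewer would widen the gap), that 6–10 is a planning range and not a limit, and that the half-widths come from the large-sample formula, which reproduces all five. It is a matter of numbers not carried through after an amendment. It affects how the registry's size and precision are described, and it does not change the planned analysis.

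**What to change.** - In *Enrollment and data collection*, change the total from 200 to 300.
- In the same paragraph, replace 6–10 per site with an average of at least about 14 per site (300 / 22 = 13.6), noting that it is higher if fewer than 22 sites enrol.
- Add one sentence saying that sites enrol consecutively until the registry total of 300 is reached. This also removes any suggestion that the per-site figure is a stopping point.
- In *Statistics*, name n = 300 and restate the half-widths: ±2.91 points at 7.1%, and ±1.93, ±2.47, ±3.24 and ±3.54 at 3.0, 5.0, 9.0 and 11.0%. If precision per valve is of interest, about 150 patients give ±4.11 points at 7.1%.

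The cost is two numbers and one sentence in the enrolment paragraph, and one stated n with five recalculated half-widths in *Statistics*. No patients are needed beyond the 300 already decided.

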**Table 1 Tab1:** **Data collection**

Parameter	Admission	Intervention	Discharge	30d FU
Inclusion/Exclusion criteria	X			
Demographics	X			
Diagnosis of valve disease	X			
Echocardiography	X			
Symptoms	X			X
Cardiac baseline characteristics	X			
ElectroCardioGram	X		X	
Comorbidities	X			
Risk scores	X			
Prior cardiovascular intervention	X			
Current medications	X		X	X
Interventional details		X		
Interventional results		X		
Adverse events		X	X	X
Hospitalization duration			X	
Creatinine value	X		X	
Early safety/Clinical efficacy				X

Information is entered directly into a secure electronic case report form (eCRF) by physicians or study nurses. Notably, the eCRF was designed to perform automatic checks for plausibility and completeness. Also, all corrections are documented and tracked. Furthermore, 20% of the sites are to be selected at random for monitoring and source data verification after completion of patient documentation. In addition, 100% source data verification will be conducted for the following serious adverse events: death, stroke, major bleeding, valve complications, vascular complications, permanent pacemaker implant, and renal failure.

### Pre-defined endpoints

The primary objective of ROUTE is overall mortality within thirty days after TAo-TAVI. Secondary objective are to determine TAVI related in-hospital and 30d mortality, complication rates as to VARC 2
[21], the identification of multivariable adjusted predictors for a poor outcome of TAo-TAVI and to further establish role of CT-technology in patient screening (valve sizing, access planning, complication prevention).

### Statistics

The sample size for ROUTE was estimated based on an overall mortality rate of approximately 7.1% at 30 days in accordance with unpublished data provided by the principal investigators. This rate can be ascertained with a 95% CI of 7.1 ± 3.56%. 95% confidence intervals are ±2.36 and ±3.02 at 3.0 and 5.0% risk respectively while they are ±3.97 and ±4.34 at 9.0 and 11.0%.

Intent-to-treat analysis, defined as all patients enrolled in the registry will be evaluated. Subjects are considered registry participants when they enter the cath lab/hybrid suite. Descriptive data summaries will be used to present and summarize the collected evaluation data. For categorical variables (e.g. gender) frequency distributions will be given. For numeric variables (e.g. patient age) minimum, maximum, mean, median and standard deviation will be calculated.

Linearized rates and actuarial probability statistics will be used when appropriate for adverse event reporting, and Kaplan–Meier plots may be employed for survival and outcome analyses.

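### The confidence-interval half-widths given for 30-day mortality are those of 200 patients, while the current target is 300, so the stated precision of the pooled primary endpoint is out of date and about 22% too wide

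*Protocol article*

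**What the plan says.** The Statistics section sets out the basis of the sample size: "The sample size for ROUTE was estimated based on an overall mortality rate" of about 7.1% at 30 days. It then gives the resulting precision, "This rate can be ascertained with a 95% CI of 7.1 ± 3.56" per cent, and the half-widths at other risks: "95% confidence intervals are ±2.36 and ±3.02 at 3.0 and 5.0% risk respectively", while "they are ±3.97 and ±4.34 at 9.0 and 11.0" per cent. It does not say how many patients these figures assume.

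Three other places give the number of patients, and they disagree:

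- Abstract, Methods/Design: "with the goal of consecutively enrolling 300 patients at up to 22 sites across Europe".
- Enrollment and data collection: "ROUTE aims at enrolling 200 consecutive patients", with 6–10 patients expected per site.
- Amendments/Notes to file, on the June 2014 change: an increase of 100, "resulting in a total of 300 enrolled patients and about 150 patients per valve".

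The primary objective, under Pre-defined endpoints, is overall mortality within 30 days. It is not split by valve. The Statistics section analyses everyone enrolled.

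**The concern.** The article contains two enrolment targets, and the only precision it states for the primary endpoint has no sample size attached. If the half-widths rest on the superseded target, they do not describe the registry being run.

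The registry has no hypothesis test, performance goal or margin, so in this article the half-width is the whole argument for the sample size. It should therefore belong to the size in force. A reader who wants to know how well 30-day mortality will be estimated now gets the wrong figure. A reader who wants to know what the extra 100 patients add to precision gets no figure.

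**Working it through.** **Inputs.** The assumed risks of 3.0, 5.0, 7.1, 9.0 and 11.0% and their half-widths come from Statistics. The candidate sizes are 200 (Enrollment and data collection), 300 (Abstract; Amendments/Notes to file) and about 150 per valve (Amendments/Notes to file).

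**Formula.** The 95% normal-approximation (Wald) half-width for one proportion is h = 1.96 × √(p(1 − p)/n).

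**Step 1: reproduce the printed figure.** At p = 0.071 and n = 200, h = 1.96 × √(0.071 × 0.929/200) = 0.0356, or ±3.56 points. This is the printed value.

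**Step 2: solve for n.** With n = 1.96² × p(1 − p)/h², the five printed half-widths give n = 200.7, 200.1, 199.9, 199.6 and 199.7. Rounding of the printed figures accounts for the small departures from 200.

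**Step 3: recompute at each size** (half-widths in percentage points).

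| Risk | Printed | n = 200 | n = 300 | n = 150 |
|---|---|---|---|---|
| 3.0% | 2.36 | 2.36 | 1.93 | 2.73 |
| 5.0% | 3.02 | 3.02 | 2.47 | 3.49 |
| 7.1% | 3.56 | 3.56 | 2.91 | 4.11 |
| 9.0% | 3.97 | 3.97 | 3.24 | 4.58 |
| 11.0% | 4.34 | 4.34 | 3.54 | 5.01 |

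**Step 4: size of the discrepancy for the pooled endpoint.** 3.56/2.91 = 1.22, which agrees with √(300/200) = 1.22. The printed interval at 7.1% runs from 3.54 to 10.66%. At n = 300 it runs from 4.19 to 10.01%.

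**Step 5: could another interval method explain ±3.56 at 300?** No. At 7.1% and n = 300 the half-width is 2.94 by Wilson, 3.07 by continuity-corrected Wald and 3.08 by Clopper-Pearson. A 90% Wald interval gives 2.44 and a 99% one gives 3.82. At n = 150 the Wilson, continuity-corrected and Clopper-Pearson values are 4.20, 4.44 and 4.45, and the 90% and 99% Wald values are 3.45 and 5.40. Of the methods and sizes tried, only plain 95% Wald at n = 200 matches all five printed figures.

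**Step 6: the per-site numbers.** The enrolment section expects 6–10 patients per site, and the article allows up to 22 sites. That gives 6 × 22 = 132 to 10 × 22 = 220 patients. The range includes 200 but not 300, which would need 300/22 = 13.6 per site on average. The per-site range therefore fits the former target only.

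**The case against.** **Nothing is miscalculated.** Every half-width is correct for 200 patients, and the amendments section openly discloses the increase. That is so: the fault is an outdated basis, not faulty arithmetic. It is still more than a difference between an amendment note and the current text, because the Abstract itself states 300 as the goal while the enrolment section states 200 in the present tense.

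**The error is harmless in direction.** For the pooled primary endpoint the printed interval is too wide. No test, margin or performance goal depends on it. This stands, and it limits how serious the point is.

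**The full protocol or the June 2014 amendment may hold a revised rationale.** It may, since neither is shown. But the article prints specific figures, and those figures do not match the target in its own Abstract.

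**Enrolment is competitive, so 6–10 per site may be an expectation and not a cap.** This is fair. Even so, the expectation was evidently set for 200 and sits in the same sentence as that target.

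**A stronger reading is tempting.** A reader might infer that the registry was enlarged in order to estimate mortality for each valve, and that ±3.56 therefore overstates the precision of each valve's estimate, which would be ±4.11 at n = 150. A reader might also infer a planned comparison of the two valves. The documents support neither. The amendments section says what the increase results in, not what it is for. Neither Pre-defined endpoints nor Statistics names a valve-specific estimate or a comparison between valves. The printed precision is offered for overall mortality only.

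**Conclusion.** The point holds as a moderate consistency correction. The five half-widths in Statistics, like the target in the enrolment section, belong to 200 patients, whereas the Abstract and the amendments section set 300. For the pooled primary endpoint at 7.1% the half-width should read ±2.91 and not ±3.56. The printed figure is about 22% too wide, which is conservative. The validity of the primary estimate is not affected.

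This rests on three assumptions: that 300 is the target in force, that all 300 contribute to the estimate (the article makes no allowance for loss), and that the normal approximation already used is kept. With Clopper-Pearson limits the half-width at 300 would be about ±3.08, still below the printed value.

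The n = 150 figures matter only if valve-specific rates will be reported, and the article does not say that they will be.

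**What to change.** 1. In Statistics, state that the precision refers to n = 300, and replace the half-widths with ±1.93, 2.47, 2.91, 3.24 and 3.54 at 3.0, 5.0, 7.1, 9.0 and 11.0%.
2. In Enrollment and data collection, reconcile the target of 200 with the 300 in the Abstract and in Amendments/Notes to file. Revise the 6–10 patients per site at the same time. Changing the target alone would leave a sentence that reaches at most 220 patients at 22 sites.
3. Only if valve-specific mortality will be reported, add the half-widths for about 150 patients per valve: ±2.73, 3.49, 4.11, 4.58 and 5.01 at the same risks. No new per-valve analysis is required by this point.

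The cost is wording only, with no patients beyond the 300 already planned and no change to the primary analysis. The pooled precision becomes more favourable than the one now printed.

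### The planned precision is given as symmetric Wald intervals at 200 patients: coverage is modestly below 95%, the upper limits sit about 0.8 to 1.1 points low at that size, and the figures do not reflect the current target of 300

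*Protocol article*

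**What the plan says.** The Pre-defined endpoints section sets the aim: "The primary objective of ROUTE is overall mortality within thirty days after TAo-TAVI". There is no comparator, hypothesis test or margin, so the mortality estimate and its interval are the main inferential result.

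The Statistics section bases the sample size on an "overall mortality rate of approximately 7.1% at 30 days" and adds: "This rate can be ascertained with a 95% CI of 7.1 ± 3.56" percent. It then gives the precision at other rates: "95% confidence intervals are ±2.36 and ±3.02 at 3.0 and 5.0% risk respectively", and "they are ±3.97 and ±4.34 at 9.0 and 11.0" percent. It names neither the interval method nor the number of patients behind these figures.

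The number of patients appears elsewhere, in two forms. Under Enrollment and data collection, "ROUTE aims at enrolling 200 consecutive patients". Under Amendments/Notes to file, the June 2014 change is described as "resulting in a total of 300 enrolled patients and about 150 patients per valve". The Abstract also gives 300.

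**The concern.** A symmetric plus-or-minus interval around a small proportion points to the normal approximation. For rates of 3% to 11% the binomial distribution is skewed. The Wald interval is then centred too low, and its standard error is too small exactly when few deaths happen to be observed. Both effects push the upper limit down.

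For a registry whose primary result is a mortality rate, the upper limit is the safety statement. An interval labelled 95% whose upper limit falls below the true rate about twice as often as it should gives a somewhat favourable picture of the mortality that the registry can exclude.

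**Working it through.** **Inputs.** Rates of 3.0, 5.0, 7.1, 9.0 and 11.0% and their half-widths come from the Statistics section. The sizes 200, 300 and 150 come from Enrollment and data collection and from Amendments/Notes to file. Intervals are two-sided 95%, z = 1.96.

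**Step 1: reproduce the printed figures.** Wald half-width = 1.96·√(p(1−p)/n). At 7.1% and n = 200: 1.96·√(0.071 × 0.929/200) = 1.96 × 0.01816 = 0.0356, or 3.56 points. The five rates give 2.364, 3.021, 3.559, 3.966 and 4.336, which match the printed values to two decimals. Solving each printed half-width for n gives 199.6 to 200.7. With n = 300 the values would be 1.93, 2.47, 2.91, 3.24 and 3.54, which do not match.

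**Step 2: coverage at n = 200.** For each true rate p, sum the binomial(200, p) probabilities of the death counts whose Wald interval contains p, and separately of those whose upper limit is below p or whose lower limit is above p.

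| True rate | Expected deaths | Coverage | Upper limit below truth | Lower limit above truth |
|---|---|---|---|---|
| 3.0% | 6 | 93.3% | 5.9% | 0.8% |
| 5.0% | 10 | 92.6% | 6.2% | 1.2% |
| 7.1% | 14.2 | 94.2% | 5.0% | 0.8% |
| 9.0% | 18 | 94.0% | 4.7% | 1.3% |
| 11.0% | 22 | 94.9% | 3.9% | 1.2% |

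Each tail should be 2.5%. Averaged over true rates from 3% to 11%, Wald coverage is 93.3% (minimum 87.8%) and the upper-limit miss is 5.6%. Wilson coverage over the same range averages 95.1% (minimum 93.4%).

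**Step 3: upper limits at n = 200.** The observed rate is set equal to the assumed rate. At 7.1% this means a fractional count, np = 14.2.

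| Rate | Wald (as printed) | Wilson | Clopper-Pearson |
|---|---|---|---|
| 3.0% | 5.36 | 6.39 | 6.42 |
| 5.0% | 8.02 | 8.96 | 9.00 |
| 7.1% | 10.66 | 11.53 | 11.59 |
| 9.0% | 12.97 | 13.78 | 13.85 |
| 11.0% | 15.34 | 16.09 | 16.18 |

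The gap is 0.75 to 1.03 points against Wilson and 0.84 to 1.06 against Clopper-Pearson. The lower limits shift upward too, so the total width at 7.1% is similar: 7.12 points (Wald), 7.24 (Wilson), 7.64 (Clopper-Pearson).

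**Step 4: the current target.** Clopper-Pearson upper limits at n = 300 are 5.62, 8.11, 10.62, 12.82 and 15.10. The printed 5.36 and 8.02 are below these by 0.26 and 0.09 points. The printed 10.66, 12.97 and 15.34 are slightly above them.

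**Step 5: what updated figures would look like at 7.1%.** Wilson centre = (p + z²/2n)/(1 + z²/n) and half-width = z·√(p(1−p)/n + z²/4n²)/(1 + z²/n). With n = 300 the centre is (0.071 + 0.0064)/1.0128 = 0.0764 and the half-width is 0.0294.

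| n | Wald | Wilson | Clopper-Pearson |
|---|---|---|---|
| 300 | 4.19–10.01 | 4.70–10.58 | 4.47–10.62 |
| 150 | 2.99–11.21 | 3.97–12.37 | 3.55–12.46 |

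**The case against.** The strongest reply is that these are planning figures. They stand in the sample-size paragraph, are correct for the usual formula, and decide nothing: no margin, test or stopping threshold depends on them, and the total width is almost the same under any method. This stands, and it is why the point is small.

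Three stronger readings are tempting, and the article does not support them.

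- *The registry will report its results with Wald intervals, including for VARC-2 complications.* The article does not fix the method for the final mortality estimate. It states no interval for complications. The reporting method may properly be set in the analysis plan or the full protocol.
- *The intervals plainly fail to cover.* At the plan's own scenario (7.1%, n = 200) coverage is 94.2%, and at 11% it is 94.9%. Coverage also oscillates with the rate: at n = 300 it is 92.9% at 7.1% but 94.98% at 7.0%, and 95.2% at 11%. Single low values should not carry the argument. The average shortfall and the lopsided tails should.
- *The printed upper limits understate mortality under the current plan.* Against exact limits for 300 patients, they do so only at 3% and 5%, and slightly. At 7.1% and above they do not, but only because they were computed for 200 patients. Updating the size while keeping Wald would bring the understatement back: 10.0% instead of 10.6% at 7.1%.

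Nor is Wilson perfect: at 9% and n = 200 its coverage is 93.8%. Its advantage is average coverage close to 95% and far fewer upper-limit misses.

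**Conclusion.** The point holds in a limited form. The printed precision figures are Wald half-widths at n = 200. As 95% intervals they cover modestly too little (a shortfall of 0.1 to 2.4 points at the five printed rates), miss mainly by understating mortality, and imply upper limits about 0.8 to 1.1 points too low for that size. They also describe a registry of 200 rather than the current 300, or about 150 per valve.

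The sample-size rationale is not undermined. The size of 200 behind the figures is inferred, since the Statistics section does not state it, but the match at all five rates leaves little doubt. The coverage results assume independent patients with a common risk and complete 30-day follow-up. The comparison of limits assumes that the observed rate equals the assumed one.

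**What to change.** In the Statistics section, replace the plus-or-minus figures with Wilson (or Clopper-Pearson) limits at the current size, state that size, and add the precision per valve. At 7.1% the Wilson limits are 4.7% to 10.6% for 300 patients (exact 4.5% to 10.6%) and about 4.0% to 12.4% for 150. Add one sentence saying that the same method will be used for 30-day mortality in the report.

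The cost is a recalculation and a sentence; design, enrolment and data collection are unaffected. The price is a less favourable upper limit than Wald at the same size: at 7.1%, about 0.6 points higher for 300 patients and about 1.2 points higher for 150.
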